### Objectives and hypothesis

The primary objective of this study is to compare the effectiveness of repeated nine sessions of anodal tDCS targeting the DLPFC combined with an intensive exercise programme to nine sessions of sham tDCS combined with the same exercise programme. The comparison will focus on pain intensity and the multidimensional impact of pain in patients with CLBP immediately after the intervention.

The secondary objectives are to assess the effects of repeated sessions of tDCS over the DLPFC combined with an exercise programme on:

Pain, disability and psychological factors:Pain intensity, multidimensional impact of pain, functional disability and psychological outcomes (including fear-avoidance beliefs, catastrophising, anxiety and depression) immediately after the intervention (week 4), with follow-ups at 12 and 24 weeks.Functional brain connectivity:Changes in functional resting-state brain connectivity as evaluated by electroencephalography (EEG) over the DLPFC and its associated neural networks, between baseline and immediately after the intervention (week 4).Neuromuscular function of the erector spinae:The restoration of the flexion–relaxation phenomenon (FRP) in the erector spinae during forward bending was assessed immediately after the intervention (week 4).

We hypothesise that anodal tDCS targeting the DLPFC, combined with an intensive exercise programme, will lead to greater improvements in all clinically measured outcomes compared with sham tDCS combined with the same exercise programme, both immediately after the intervention (week 4) and at the 12- and 24-week follow-ups. Regarding functional brain connectivity, we hypothesise an increase in DLPFC connectivity with associated areas, and for the neuromuscular function, a restoration of FRP in the erector spinae muscles. Further, the magnitude of these neurophysiological changes will correlate with clinical improvements.

This protocol is version 1.0, dated 12 February 2026.

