#### Neurophysiological outcome

Spontaneous activity in a task-free state will be assessed using a 10-min resting-state EEG.

EEG data will be continuously acquired at 512 Hz using an Active II EEG system (Biosemi, Amsterdam) with 128 pre-amplified (active) EEG channels with standard 10–20 configuration. Participants will be asked to keep their eyes closed and remain relaxed yet awake. Epochs showing artefacts or reduced vigilance were removed following visual inspection. From the remaining data, 5 min free of artefacts were re-referenced to the common average. Source-level functional connectivity (FC) will be computed in MATLAB (The MathWorks, Natick, Massachusetts, USA) using the open-source NUTMEG toolbox and its Functional Connectivity Mapping module, as previously described. Lead fields on a 10 mm grid will be generated with a boundary element model derived from an individual template 3D T1-weighted MRI (Helsinki BEM Library) via the NUTMEG plugin. Artifact-free EEG epochs will be band-pass filtered between 1 and 20 Hz using a zero-phase elliptic filter and projected to grey-matter voxels with an adaptive spatial filter (scalar minimum-variance beamformer).

Connectivity metrics will be computed separately in seven canonical bands—delta (1–3 Hz), low theta (4–5 Hz), high theta (6–7 Hz), low alpha (8–10 Hz), high alpha (11–12 Hz), low beta (13–16 Hz) and high beta (17–20 Hz). Because between-subject differences in synchronisation magnitude can reflect variations in signal-to-noise ratio, we will normalise each participant’s connectivity map within band by subtracting the subject’s mean Weighted Node Degree (WND) across all cortical voxels and dividing by the corresponding SD, yielding voxelwise z-score maps. The z-maps will then be spatially normalised to canonical MNI space using SPM8 functions (http://www.fil.ion.ucl.ac.uk/spm/software/spm8/).

Relationships between the clinical variables and NIBS-induced changes in effective connectivity/FC will be analysed with Pearson correlations and corrected with a false discovery rate of 5%.

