### Sample size calculation

An a priori sample size calculation was conducted using G*Power software (V.3.1.9.4). The estimation was based on the Minimal Clinically Important Improvement for the COMI, considered the primary outcome measure, with a reference value of 2.6 points.^47^ This endpoint was defined as the difference in COMI scores between baseline and immediately postintervention (week 4).

The expected SD of the COMI score in both groups was conservatively estimated at 3, based on a previous study^48^ and expert clinical judgement. With a significance level (α) of 0.05 (two-tailed) and a desired statistical power of 80% (1−β), the required sample size was calculated to be 22 participants per group to detect a clinically meaningful between-group difference.

To account for an anticipated dropout rate of 10%, the recruitment target was adjusted to 24 participants per group. Therefore, a total of 48 participants will be enrolled in this trial.

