#### Neurophysiological outcome

To determine neurophysiological differences between treatment groups (stimulation vs sham), unpaired pseudo-t-tests or their non-parametric equivalents will be conducted, depending on the distribution of the EEG variables of interest. EEG parameters will be analysed both on a voxelwise basis and within predefined regions of interest, with or without correction for multiple comparisons.

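### The Pearson correlations between clinical variables and connectivity change have no term for arm and no stated analysis set; if both arms are pooled, arm differences alone can produce a correlation

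*Protocol article*

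**What the plan says.** Objectives and hypothesis makes three statements that bear on this point. Active stimulation with exercise "will lead to greater improvements in all clinically measured outcomes compared with sham tDCS" given with the same exercise. For the brain, "we hypothesise an increase in DLPFC connectivity with associated areas". It adds that "the magnitude of these neurophysiological changes will correlate with clinical improvements".

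The method for that last hypothesis stands at the end of the Neurophysiological outcome text under Outcomes. The subject there is "Relationships between the clinical variables and NIBS-induced changes in effective connectivity/FC". The stated method is that these "will be analysed with Pearson correlations and corrected with a false discovery rate of 5" per cent.

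Under Statistical analysis, the Neurophysiological outcome text plans a separate comparison of the arms: "To determine neurophysiological differences between treatment groups (stimulation vs sham), unpaired pseudo-t-tests" or non-parametric equivalents. EEG is recorded in both arms at baseline and week 4.

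No section says whether the correlation uses both arms, each arm separately or the active arm only. No section adjusts or stratifies it by arm.

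**The concern.** The hypothesis concerns individuals: participants whose connectivity changes more should improve more. A two-variable correlation over both arms mixes that within-arm association with the difference between the arm means. If stimulation shifts both connectivity and symptoms, the active participants sit in one corner of the scatter plot and the sham participants in the other. A correlation then follows even if no association exists within either arm. The artefact is largest when the treatment works on both variables, which is also when a mechanistic reading is most attractive.

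FDR control does not cure this. It limits false discoveries among p-values that test the intended null, whereas a pooled p-value tests a null that an arm effect on both variables already breaks.

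At stake is the interpretation of the only stated test of the connectivity-symptom link. A pooled result could be reported as connectivity change tracking improvement when it only restates that both differ by arm.

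**Working it through.** **Inputs from the article.** COMI difference: "with a reference value of 2.6 points". Spread: "The expected SD of the COMI score in both groups was conservatively estimated at 3". Two-sided α 0.05, power 80%, 22 evaluable per group, 24 per group recruited, 1:1 allocation. The standardised COMI difference is 2.6/3 = 0.867.

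**Input that the article does not give.** No effect size is stated for connectivity. It is an assumption here, run from 0 to 1.5 SD.

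**The plan's own figure.** The article gives no figure for the correlation. For the primary outcome, a two-sample t-test with d = 0.867 has power 0.782 at 21 per group and 0.802 at 22 per group. The stated 22 is reproduced, so 0.867 SD is the right planning effect to carry forward.

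**Induced correlation, both arms pooled.** Take zero association within each arm, equal arms, within-arm SD 1, and arm differences d1 (connectivity) and d2 (clinical):

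r = (d1·d2/4) / √[(1 + d1²/4)(1 + d2²/4)]

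With d1 = d2 = 0.867, d1·d2/4 = 0.188 and r = 0.188/1.188 = 0.158.

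**Rejection rate.** 40,000 simulated trials per setting, 22 per arm, d2 = 0.867, nominal two-sided 5% per test, before FDR:

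| Assumed d1 (SD) | Induced r | Pooled Pearson | Partial, given arm | Active arm only |
|---|---|---|---|---|
| 0 | 0.00 | 5.1% | 5.0% | 5.0% |
| 0.5 | 0.10 | 9.5% | 5.1% | 5.0% |
| 0.867 | 0.16 | 17.8% | 5.1% | 4.9% |
| 1.2 | 0.20 | 27.3% | 5.0% | 4.9% |
| 1.5 | 0.24 | 35.9% | 5.2% | 5.0% |

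A Fisher z calculation at n = 44 with d1 = d2 = 0.867 gives 17.4%, in line with the simulation. With 24 per arm the pooled rates are 4.9%, 10.0%, 19.4%, 29.5% and 38.6%. With only 0.5 SD on both variables and 22 per arm, r is 0.06 and the rate is 6.6%.

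**After the FDR step.** The number of tests in the FDR family is not stated. As an illustration, assume seven independent tests (one per frequency band), Benjamini-Hochberg at 5%, 22 per arm, 0.867 SD on COMI and on each affected band, and no within-arm association. If one band differs by arm, the rejection rate for that band falls to about 5%, and the chance of at least one rejection is about 9%. If all seven differ, the figures are about 7% per test and about 28%. Correction lowers the per-test rate but does not remove the artefact.

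**Active arm only.** The smallest r detectable with 80% power is tanh[(1.960 + 0.842)/√(n − 3)].
- n = 22: tanh(2.802/4.359) = 0.57
- n = 44: tanh(2.802/6.403) = 0.41

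Adjusting for arm replaces n − 3 by n − 4, which gives 0.42 at n = 44. The comparison assumes the same association in both arms and ignores FDR.

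**The case against.** The strongest reply is that the article never says the arms are pooled. It speaks of changes induced by the stimulation, and the Sham tDCS section describes the sham as having no significant neurophysiological effect. An active-arm or within-arm analysis is therefore a fair reading, and on that reading the error rate is correct. This stands. A reader might infer that a pooled analysis is planned and that a spurious correlation is expected. The text supports neither.

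Second, 17-18% is a per-test rate before the FDR step that the article prescribes, and it borrows the COMI planning effect for connectivity. This stands too. The figure is conditional: with no arm effect on connectivity the rate is 5%.

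Third, the sentence on correlations speaks of clinical variables, not clinical change. If baseline variables were meant, randomisation would give no expected arm difference and hence no artefact. The stated hypothesis makes change the likelier intent, but the wording does not settle it.

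Fourth, the article calls secondary outcomes exploratory, and analysis sets are often left to an analysis plan. This limits the weight of the point but does not remove it. The article does not leave the method open: it names a two-variable correlation, which cannot carry arm.

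Finally, a reader might take this correlation as the only test of the whole mechanism hypothesis. It is not. Connectivity is also compared between arms, and the flexion-relaxation ratio is tested before against after. The correlation is the only stated test of the connectivity-symptom link.

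**Conclusion.** The point holds in a conditional form. The article names a simple Pearson correlation, gives it no term for arm and does not say which arms enter.

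- **Both arms pooled:** if both variables differ by arm, as the trial's hypotheses lead one to expect, a correlation arises without any within-arm association. With a COMI difference of 0.867 SD and an assumed connectivity difference of 0 to 1.5 SD, r is 0 to 0.24 and per-test rejection before FDR is 5% to 36%. At the planning effect on both variables the inflation is modest.
- **Active arm only:** the test is valid. The cost is precision, with a detectable r of about 0.57 against about 0.41 if the association is the same in both arms.

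An arm-adjusted correlation over both arms avoids both problems. It is worth changing, but the analysis is exploratory and the primary COMI conclusion does not depend on it.

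**What to change.** In the Neurophysiological outcome text under Outcomes:

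1. State that the correlation uses clinical change and connectivity change from baseline to week 4, in participants of both arms.
2. Replace the simple Pearson correlation with a partial correlation adjusted for arm. A regression of clinical change on connectivity change with arm as covariate tests the same association. Adding the baseline clinical score is optional, but it is a different model and should be named as such if chosen.
3. Report the within-arm correlations descriptively, so that a link present only under active stimulation can be seen.
4. Keep the 5% FDR.

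The cost is a change of wording and one degree of freedom (a second if the baseline score is added). Visits, measurements and sample size stay as they are.

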#### Neuromuscular outcome

The FRP corresponds to a myoelectric silence of erector spinae during maximal forward bending. The FRP is reduced or abolished in approximately half of individuals with LBP.^44^

It will be assessed at baseline and post-intervention (week 4) to evaluate potential restoration. A sEMG system (model Trigno, Delsys, Boston, Massachusetts, USA) will be used with a sampling frequency of 1000 Hz. The skin at the electrode sites will be shaved, abraded and cleaned with alcohol, prior to data collection. Electrodes will be placed over the left and right longissimus dorsi (at the level of the L1 spinous process) and the left and right multifidus muscles (at the L5 level) aligned with the orientation of the muscle fibres and according to the recommendations of the Surface Electromyography for Non-Invasive Assessment of Muscles projects.^45^ Standardised instructions will be provided to all participants to ensure consistency in movement execution. Participants will be instructed to stand upright with their arms relaxed at their sides, eyes directed forward and level. They will then be asked to bend forward into maximal trunk flexion while maintaining their knees fully extended, allowing the upper body and arms to hang freely in a relaxed manner.

The movement sequence will be divided into four distinct phases, each lasting five seconds^46^: (1) static upright standing, (2) forward bending into full flexion, (3) static maintenance of full flexion and (4) return to the initial upright standing posture. Specifically, participants will first maintain a neutral standing position for 5 s, followed by a controlled descent into maximal forward flexion over 5 s. They will then hold the fully flexed position statically for an additional 5 s before returning to the starting posture over the final 5 s.

To ensure correct execution, an experimenter will demonstrate the movement sequence and pacing prior to the trials. A metronome will be used to regulate timing and promote temporal consistency across participants. Each participant will perform three consecutive trials per set, and the entire sequence will be repeated twice.

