### Participants

The study will include two groups of 24 adult participants, aged 18–65 years, all diagnosed with CLBP, defined as pain localised in the lower back, with or without radiating leg pain, persisting for more than 3 months. Potential participants will be recruited through various networks, including social media campaigns, referrals from physicians or physiotherapists and word of mouth. To be eligible, participants must report an average pain intensity of at least 3 out of 10 on the pain numerical rating scale (NRS) over the past week, with 0 representing ‘no pain’ and 10 representing ‘worst pain imaginable’. Additionally, they must have sufficient cognitive abilities to complete the study questionnaires, demonstrated by a minimum B2 level in French. Exclusion criteria include neuropathic pain (DN4 score ≥4),^37^ radiating pain beyond the knee, sensory or motor deficits of the lower limb, a specific cause of low back pain (eg, inflammatory rheumatic disease or fibromyalgia), lumbar surgery involving instrumentation, herniectomy within the previous 6 months, major neurological or psychiatric disorders, pregnancy and any contraindication to tDCS (eg, epilepsy, pacemaker, metal implants in the skull or skin lesions at electrode sites).

No specific contraindications to exercise were applied beyond the general eligibility criteria. A complete list of inclusion and exclusion criteria is provided in online supplemental material 2.

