#### Neuromuscular outcome (FRP)

The root mean square (RMS) of the EMG signals will be calculated using a sliding window of 1 s with a step size of 50 ms.^50^

The three phases of the flexion-extension cycle—flexion, relaxation and extension—will be manually identified on the RMS signal, and the peak value for each phase will be recorded.

The flexion–relaxation ratio (FRR) will be computed by dividing the peak EMG activity during the flexion phase by that of the relaxation phase. Preintervention and postintervention FRR values will be compared using a paired t-test to assess statistical significance. If the assumption of normality is not met, the non-parametric Wilcoxon signed-rank test will be applied instead.

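### The flexion–relaxation aim is restoration, but the analysis takes the raw ratio in everyone, with no definition of impaired or restored and no analysis by baseline status

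*Protocol article*

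**What the plan says.** The Protocol article, Objectives and hypothesis, expects "for the neuromuscular function, a restoration of FRP in the erector spinae muscles". The Neuromuscular outcome section under Outcomes repeats that purpose: "It will be assessed at baseline and post-intervention (week 4) to evaluate potential restoration". It describes an intact FRP as electrical silence of the erector spinae in full forward bending, and states that "The FRP is reduced or abolished in approximately half of individuals with LBP".

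The eligibility text under Participants selects on diagnosis, age and pain ("participants must report an average pain intensity of at least 3 out of 10 on the pain numerical rating scale (NRS) over the past week") and names no FRP criterion. It adds that "A complete list of inclusion and exclusion criteria is provided in online supplemental material 2"; that supplement is not shown.

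The Neuromuscular outcome (FRP) section of the statistical analysis defines the measure: "The flexion–relaxation ratio (FRR) will be computed by dividing the peak EMG activity during the flexion phase by that of the relaxation phase". It then fixes a paired t-test of pre- and post-intervention FRR, or a Wilcoxon signed-rank test if normality fails. It gives no value of FRR that separates impaired from intact, no definition of restored, no subset and no adjustment for baseline FRP. The Secondary analysis section labels secondary outcomes exploratory.

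**The concern.** Restoration is possible only where the phenomenon is impaired. By the protocol's own figure, carried over to this sample, about half the participants have nothing to restore. A mean FRR change over everyone therefore mixes people who can show the effect with people who cannot. It can also rise without any impaired participant becoming normal, so it does not measure restoration.

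The scale may make this worse. Relaxation-phase activity is the denominator, so the participants with an intact FRP have the smallest denominators and the largest ratios. Small changes in near-silent activity move those ratios a great deal.

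At stake is the mechanistic reading of the trial, since the Discussion relies on FRP to help explain how the treatment works. A partial improvement in the impaired could be missed, or a shift in participants who were normal at baseline could be read as recovery. That the planned paired test does not compare the arms at all is a separate defect. Replacing it with a between-arm test would not remove the dilution.

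**Working it through.** **The plan's own figure.** The sample size is for COMI, not FRP. With 2.6/3 = 0.867 SD, two-sided 5% and 80% power, a two-sample t-test needs 21.9, so 22 per group (power 80.2%). This reproduces the stated 22. The article gives no FRR mean, SD or power, so every FRR input below is an assumption.

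**How many are impaired.** With share p = 0.5 (Neuromuscular outcome section) and 48 enrolled:
- in total 0.5 × 48 = 24, binomial 95% range 17 to 31;
- per arm 0.5 × 24 = 12, range 7 to 17.

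**Dilution.** If the change in the impaired is δ and in the others zero, the mean over everyone is p × δ, which is δ/2 at p = 0.5. With equal SD σ in both subsets, the between-arm noncentrality is
- everyone: 0.5δ / (σ√(2/24)) = 1.73 δ/σ;
- impaired only: δ / (σ√(2/12)) = 2.45 δ/σ.

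The ratio is 2.45/1.73 = 1.41, so restricting to the impaired gains despite halving n. As a scale for the loss, halving 0.867 SD to 0.433 SD raises the requirement at 80% power from 22 to 85 per group.

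**Power by noncentral t.** Assume 0.8 SD in the impaired, none in the others, and 22 completers per arm.

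| Test (p = 0.5) | Everyone | Impaired only |
|---|---|---|
| Paired, one arm (22 vs 11) | 38% | 67% |
| Paired, both arms pooled (44 vs 22) | 67% | 95% |
| Between arms (22 vs 11 per arm) | 25% | 43% |

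The between-arm figures add no mixture variance. For the paired test in one arm, p = 0.4 gives 27% against 56%, and p = 0.6 gives 52% against 75%. For effects of 0.5 to 1.0 SD and p of 0.4 to 0.6, the impaired-only analysis had the higher power in every case computed.

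**Power on the ratio itself, by simulation.** Assume 24 per arm, half impaired, typical baseline FRR 1.5 if impaired and 6 if intact, between-person baseline log SD 0.3, log-change SD 0.4, and an effect of 0.4 log units in impaired participants of the active arm only. Between-arm t-tests give:
- raw FRR, everyone: about 11%;
- log FRR, everyone: about 35%;
- log FRR, baseline FRR below 3: about 64%.

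Type I error stays near 5%, and the ordering holds from 40% to 80% impaired. A separate run of this model gave 10/37/59% at half impaired, 7/25/47% at 40% and 15/49/69% at 60%.

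**Where the raw variance comes from.** With equal log-change SD, raw change scales with the baseline level. The variance ratio of intact to impaired is then about (6/1.5)² = 16, and the intact half supplies roughly 16/17 = 94% of it; simulation gives about 91%. This follows directly from the assumed 1.5 and 6.

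**Size of the effect simulated.** 0.4 log units moves FRR from 1.5 to 1.5 × e^0.4 = 2.2, still below the assumed cut-off of 3. It is partial improvement. For full restoration (1.5 to 6, or ln 4 = 1.39 log units), between-arm power in everyone is about 79% to 83% on raw FRR and 95% or more on log FRR. For a move only to the cut-off (1.5 to 3), raw between-arm power is about 25% to 28%.

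**The case against.** A reader might infer that the trial could miss the effect even if every impaired participant were restored. The figures do not support that: full restoration would be found about four times in five on raw FRR and nearly always on the log scale. The loss concerns partial improvement.

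A reader might also take 11% as the power of the planned test. It is not. The article plans a paired test, which within the active arm has about 34% under the same assumptions. A rank-test fallback would lift the raw between-arm figure to about 16%. Much of the gain from 11% to 64% comes from the log scale (to 35%) rather than from selecting on baseline.

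That intact participants supply most of the variance is a consequence of the assumed FRR values. The article documents only the near-silent denominator, which makes the direction likely. The √2 gain assumes equal variances, so the two arguments should not be added together.

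The figure of about half refers to people with low back pain in general. The share in this chronic sample with pain of at least 3 is unknown. The full eligibility list is not shown, though nothing in the text suggests selection on FRP. FRP impairment is also graded, so a continuous FRR in all participants is a legitimate analysis.

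Finally, a cut-off or subset could sit in an analysis plan that is not shown. That carries some weight. But the article does fix the FRP analysis in detail, down to window, ratio, test and fallback, and the analysis it fixes does not measure restoration.

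**Conclusion.** The point holds in a limited form. The stated aim is restoration. The analysis as written averages raw FRR over everyone, never defines impaired or restored, and dilutes an effect confined to the impaired by roughly their share, about one half on the protocol's figure. The attenuation follows from arithmetic if intact participants do not change. Its cost in power depends on assumed FRR values: for a partial improvement, between arms, about 11% raw, 35% log and 64% log in the impaired. Full restoration in every impaired participant would probably still be seen. The documents do not establish that the trial would miss restoration or that enrolment was wrong. FRP is an exploratory mechanistic outcome and the main conclusion rests on COMI, so this is an improvement to consider rather than a fault that threatens the trial.

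**What to change.** In the Neuromuscular outcome (FRP) section of the statistical analysis:

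1. Analyse FRR on the log scale, between arms, adjusted for baseline log FRR, in all participants.
2. Fix before unblinding an FRR cut-off that separates impaired from intact, with its justification. The article supplies none; the value 3 used above is only an assumption for the calculation.
3. Pre-specify, as the analysis that addresses restoration and labelled exploratory, a between-arm comparison in participants impaired at baseline: change in log FRR, and the proportion moving from impaired to intact.

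Baseline FRP is already measured in everyone, so no new data and no enrolment restriction are needed. The costs are a small subset, about 12 per arm (range about 7 to 17) before dropout, and the need to settle the cut-off in advance, since one chosen after unblinding would be data-driven.
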